#### Sample size estimation

Because no previous study has examined circulating EVs in relation to MBIs and cancer, we could not use a specific effect size in estimating the sample size. Nonetheless, a recent systematic review examining the effects of Internet-based MBIs on psychological distress (anxiety and depression) found a median Cohen’s *d* value between 0.38 and 0.42 for the other primary outcome, psychological distress [14]. By using G*Power-3.1 statistical software [82] and considering repeated-measures ANOVA related to within-between interaction (group × time interaction), with an alpha significance level of 0.05 and an effect size of 0.38 (as calculated in [83]), a sample of 84 participants would allow for a power of 0.80. Additionally, previous studies showed dropout rates ranging from 12.1 to 32% for the intervention group and from 6 and 17.4% for the control group, when considering the period immediately following the intervention [23, 32, 40, 47, 49, 52, 84]. At follow-up, dropout rates were about 30.8% in the intervention group and 19.6% in the control group [52]. Considering the highest dropout rate (32%), 27 participants should be added to the estimated sample, resulting in a minimum of 111 participants to be included in the study.

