### Outcome measures

The primary and secondary outcomes collected via self-report measures are briefly described and summarized in Table 3. In short, primary outcomes are CNS-EV cargo (objective measure) and psychological distress (self-report measure). Secondary outcomes include self-reported psychosocial and health-related measures (quality of life; fear of cancer recurrence; emotion suppression; mindfulness abilities; sleep quality; posttraumatic growth; health-related behaviours; perceived social support) and a variety of biomarkers (IL-1; IL-6; IL-8; IL-10; IFN-γ; TNF; C-reactive protein; CA 15-3; PSA; CEA; adrenocorticotropic hormone; erythrocytes; glycosylated haemoglobin).

**Table 3 Tab3:** Summary of self-report primary and secondary outcomes, respective assessment measures, and screening measures

Outcome	Measure	Brief description
Primary		
Psychological distress	Depression Anxiety Stress Scales-21 (DASS-21 [100]; EP version by [101])	It is a public domain instrument that evaluates negative affective states, being one of the available measures to assess psychological distress [102, 103]. It is also used in RCTs of manualized MBIs in the oncological context [104]. It is an abbreviated version of the original version of 42 items and can be administered to people aged 18 or more. It comprises 21 items, 7 measuring depression, 7 measuring anxiety, and 7 measuring stress. Specifically, participants are required to rate each item on a 4-point Likert-type scale as reference to how they have been feeling during the last week. The rating scale varied between 0 and 3, in which 0 represents “did not apply to me at all” and 3 represents “applied to me very much or most of the time”. The score for each subscale is obtained by summing the respective 7 items, whose result range between 0 and 21. In this study, a total score will be used by summing all items, with higher scores being indicative of higher self-reported negative affective experiences. The EP version yielded satisfactory internal consistency and convergent and discriminant validity [101]).
Secondary		

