**Table 4 Tab4:**
[figure not shown]
Schedule of enrolment, interventions, and assessments

*Note*. *BaSIQS* Basic Scale on Insomnia complaints and Quality of Sleep, *CA* cancer antigen, *CCI* Client Change Interview, *CEA* carcinoembryonic antigen, *CORE-OM* Clinical Outcome Routine Evaluation - Outcome Measure, *CRP* C-reactive protein, *DASS-21* Depression, Anxiety Stress Scales-21, *DT* distress thermometer, *ERQ* Emotion Regulation Questionnaire, *FCR-7* 7-item Fear of Cancer Recurrence, *FFMQ* Five-Facet Mindfulness Questionnaire, *FTND* Fagerström Test for Nicotine Dependence, *IFN-γ* interferon gamma, *IL* interleukin, *IPAQ-SF* International Physical Activity Questionnaire - Short Form, *MBCT* mindfulness-based cognitive therapy, *PSA* prostate-specific antigen, *PTGI* Posttraumatic Growth Inventory, *SSSS* Satisfaction with Social Support Scale, *TAU* treatment as usual, *TNF* tumour necrosis factor, *W* weeks, *WHOQOL-Bref* World Health Organization Quality of Life – Bref

For each self-report measure, the total score obtained for scale and/or subscales will be used as outcomes. Measures examining the eligibility criteria and the sociodemographic and health-related information are also reported in Table 3.

To determine EVs cargo, total EVs will be isolated from platelet-free plasma samples by ultracentrifugation, followed by a purification step for CNS-derived EVs by immunoprecipitation with CNS-specific antibodies. Since we are interested in CNS-derived EVs, brain-related microRNAs will be measured to verify the origin of the EVs. This is achieved by isothermal nucleic acid amplification method. Results are measured by luminescence.

To evaluate the biochemical markers, inflammatory response biomarkers (IL-1, IL-6, IL-8, IL-10, IFN-γ, TNF) will be detected in serum by multiplex immunoassay (MILLIPLEX® Multiplex Assays Using Luminex®). Similarly, various cancer antigens (CA 15-3 and CA 19.9 in units/mL, PSA in ng/mL, CEA in ng/mL) will also be detected by immunoassay to monitor cancer recurrence. Other health-related biomarkers will include c-reactive protein (mg/L), telomerase activity, erythrocyte number (million/mm^3^), adrenocorticotropic hormone (pg/mL via immunoassay analyser), and glycosylated haemoglobin (mmol/mol via high-performance liquid chromatography).

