### Statistical methods

Screening data for errors and missing values is the first step in the data analysis plan. Missing data will be managed and avoided during the data collection by using mandatory fields in the online surveys and retrieving the data from participants when possible. Data from participants who completed fewer than 4-weekly online MBCT sessions will not be considered further, as four sessions were set as the minimum number required for participation [14].

For each group (MBCT and TAU), a summary of baseline sociodemographic and health data will be provided, including number and percentages, mean, standard deviation, median, first and third quartiles, minimum and maximum. Using the sociodemographic and health data, as well as the primary and secondary measures, comparisons will be made between groups to examine whether there are differences between groups at baseline. Similarly, differences at baseline between participants who will complete the study and those who will drop out will be examined. The presence of differences in variables may warrant the need to examine and/or adjust for their influence on outcome changes in the primary analyses. This summary also presents the within-group effect sizes (Cohen’s *d*—equation 11.10, from [135]) for each outcome across time (i.e. T1 to T2; T1 to T3; T1 to T4; T1 to T5).

The total scores of each primary and secondary measure will be used as outcomes in multiple linear mixed models (LMMs). Each model will include the interaction between group and time, while participants will be treated as a random effect. The visual inspection of Q-Q plots will be conducted to check the normal distribution of residuals. Examination of factors such as sex, type of cancer, and cancer stage will be approached by running separate models for each factor. LMM analyses can be employed using, for instance, lmer4 [136] and lmerTest [137] in R software [138].

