Furthermore, given the novelty behind this study, the sample size of the objective primary outcome could not be adequately estimated for EV studies. Therefore, the current study may be underpowered to detect the effects of internet-based MBCT on circulating EVs. This problem could be compounded by difficulties with adherence and retention in this study, given the time and other specific demands of mindfulness practice [33]. With this concern in mind, specific strategies to mitigate dropouts were identified. Also, the qualitative methods proposed in this study might be useful in this regard.

The control data is obtained here by following TAU. This control condition was selected considering the available resources, the time window for conducting this clinical study, the previous use in online MBI studies [46, 48, 52, 53, 84, 89], and the desire for a year of follow-up comparison data (hence precluding a short waitlist period for the control group). We are aware that this approach does not allow control of specific (e.g. psychoeducational aspects) and nonspecific effects (e.g. group interactions and support; closer supervision; interaction with mental health professionals) [90]. An active control or even a comparison with another established intervention would be preferable, if possible [13, 90]. However, passive control conditions have been the most common in digital MBI research to date. As the field evolves, active control conditions are likely to become more common, as suggested by studies comparing face-to-face MBIs with Internet-based MBIs [31, 41, 42, 54, 84, 89] or studies using psychoeducational intervention as a comparison [32, 40].

Considering the challenges and limitations discussed earlier, it is important to say that not all scenarios are predictable. Therefore, the possibility of overcoming the challenges by adopting new or adapted strategies that may prevent the difficulties encountered throughout this study is anticipated, in a manner that provides valuable insights into health-related and psychosocial gains fostered by internet-based MBCT in an oncology context.

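### Two primary outcomes have no testing order or success rule while the whole 0.05 is used to size distress, and the EV primary has no usable readout definition

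*Protocol article*

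**What the plan says.** Under Outcome measures, the "primary outcomes are CNS-EV cargo (objective measure) and psychological distress (self-report measure"). The Abstract and the end of the Introduction also name both. None of these places ranks the two outcomes or says whether one or both must succeed.

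The sample size section sizes distress only, using "repeated-measures ANOVA related to within-between interaction (group × time interaction"), "with an alpha significance level of 0.05 and an effect size of 0.38". It concludes that "a sample of 84 participants would allow for a power of 0.80", and adds 27 for dropout to reach 111. For EV cargo the Discussion concedes that "the sample size of the objective primary outcome could not be adequately estimated for EV studies".

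Under Statistical methods, "The total scores of each primary and secondary measure will be used as outcomes in multiple linear mixed models (LMMs"), and "Each model will include the interaction between group and time, while participants will be treated as a random effect". No other significance level appears in the article.

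Distress is measured at T1 to T5, and blood is taken at T1, T3 and T4. On the EV assay, the text after Table 4 says that "brain-related microRNAs will be measured to verify the origin of the EVs". The Blinding section says that the data analysts are not blinded, and that the EV characterisation team is blinded where possible.

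**The concern.** There are two separate difficulties.

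**Two ways to succeed.** The Discussion presents the EV question and the psychosocial question as two motivations for the trial, and it expects to confirm a role for CNS-derived EVs. EV cargo therefore carries a claim of its own. With two primary tests, no order and no joint rule, a report could call the trial positive on whichever outcome reached 0.05. The chance of at least one false positive would then exceed the 5% at which the trial was sized.

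**An EV endpoint that the analysis rule does not fit.** The models take total scores. DASS-21 has one; EV cargo does not. The microRNAs are mentioned in the plural and for a quality-control purpose. The EV primary could therefore be selected from several readouts after the data are seen, by analysts who know the allocation. Each further candidate readout would add to the error rate.

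**Working it through.** **Step 1. Reproduce the stated 84.**
Inputs from the sample size section: group-by-time interaction, alpha 0.05, power 0.80, effect size 0.38. The article does not give the number of visits, the conversion to f or the noncentrality form. I assume 2 groups, m = 5 visits, f = d/2 = 0.19 and λ = f²·N·(m−1).
- df1 = (2−1)(5−1) = 4; df2 = (84−2)·4 = 328; λ = 0.0361 × 84 × 4 = 12.13.
- Power is 0.795 at N = 83 and 0.801 at N = 84, so 84 is the smallest N that reaches 0.80.

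The figure is thus matched by a 4-df omnibus test on distress at the full 0.05. Other settings can also give 84 (for example two visits, correlation 0.25 and λ = f²·N·m/(1−ρ)), so the match is consistent with this reading but does not prove it.

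**Step 2. Error rate with two primaries.**
- Independent tests, success on either: 1 − 0.95² = 0.0975.
- Upper bound under any dependence: 0.05 + 0.05 = 0.10.
- Null simulation with 84 participants and 20,000 runs, distress at five visits and EV at three:

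| Residual correlation between outcomes | Distress test alone | EV test alone | Either | Both |
|---|---|---|---|---|
| 0 | 0.050 | 0.051 | 0.097 | 0.003 |
| 0.5 | 0.049 | 0.047 | 0.090 | 0.006 |
| 0.8 | 0.050 | 0.049 | 0.085 | 0.015 |

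Each omnibus test holds about 5% however many visits it spans. The excess comes only from having two outcomes of which either may count. If both were required, the rate would be at most 5%.

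**Step 3. Compare remedies by what they cost the sized test (formula of Step 1).**
- Bonferroni, 0.025 each: familywise error 1 − 0.975² = 0.0494 if independent. Power for distress at N = 84 falls from 0.80 to 0.71, and N would rise to 99 (100 for equal arms).
- Fixed sequence, distress first at 0.05: familywise error at most 5%. Power for distress is unchanged.
- Replacing the interaction test by one T3 contrast at d = 0.38: N = 4(1.96 + 0.84)²/0.38², about 218 in total. At N = 84 the noncentrality is 0.38 × √(84/4) = 1.74, and power is 0.41. With baseline adjustment the effect becomes 0.38/√(1−ρ²): 0.439 at an assumed ρ = 0.5 (power 0.51) and 0.532 at ρ = 0.7 (power 0.67).

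**Step 4. The EV definition.** Set side by side, the Statistical methods section requires a total score for every primary measure. The assay description offers none, and it names microRNAs only as a check of origin. The two passages do not yield one analysable EV variable.

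**The case against.** The strongest reply is that this is mostly silence. A testing order, a success rule and a locked EV readout are often placed in an analysis plan or full protocol, and neither is shown. No sentence says that EV cargo will be tested at 0.05 or that one significant outcome makes the trial positive. The authors also say openly that EV cargo has no prior effect size and may be underpowered. This part stands as a limit: the error rate is conditional on an either-outcome reading, and 0.05 for EV cargo is inferred. It does not dispose of the point. The article itself declares two primaries, uses all of its only alpha on one, and gives an outcome rule that cannot apply to the other. A both-must-succeed rule would remove the excess, but none is stated, and it fits poorly with an outcome admitted to be possibly underpowered.

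A reader might go further and infer that four post-baseline visits for distress and two for EV cargo multiply the error, giving 1 − 0.95⁶ = 26%. The document does not support that. It plans one interaction per measure, which is a single test, and no visit-by-visit comparisons between arms. The within-group effect sizes for each interval belong to a descriptive summary. Even if every visit were tested, the simulation gives about 20% to 24%, because repeated measures are correlated. Nor is the non-directional nature of the interaction test an error in itself; it means only that the direction must be read from the estimates.

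On selection of readouts, the EV laboratory team is to be blinded where possible. That protects the measurement. It does not fix which readout is primary, and the analysts remain unblinded.

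**Conclusion.** The point holds in a limited form. If either primary outcome can carry the trial at 0.05, the familywise error is about 8% to 10%: 9.75% if independent, 8.5% at a residual correlation of 0.8, and never above 10% for two tests. This rests on two assumptions that the article does not state: that EV cargo is tested at 0.05, and that one success suffices. It also counts EV cargo as a single test, which the article does not secure; several candidate readouts would raise the figure by an amount that cannot be computed from the text.

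The mismatch between the total-score rule and EV cargo needs no such assumption; it is in the text. Both matters should be settled before EV data are linked to allocation. Neither undermines the distress analysis taken alone, which keeps its 5% level.

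**What to change.** State a fixed testing sequence in the protocol, the analysis plan and the registry entry:

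1. Test the DASS-21 total group-by-time interaction, as sized, at 0.05.
2. Only if it is significant, test one named EV-cargo readout at 0.05. Define its unit, scale and model, and lock it before EV data are linked to allocation.
3. Report between-arm differences with 95% confidence intervals at each visit for both outcomes where measured, with T3 as the named contrast for interpretation. Direction of effect is read from these.
4. Label all other EV readouts exploratory, and reword the total-score sentence so that it covers EV cargo.

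The interaction test should not be swapped for a single T3 contrast unless the sample size or power is restated. On the protocol's own 0.38 and 84 participants, power would drop from 0.80 to about 0.41 unadjusted, or 0.51 to 0.67 with baseline adjustment at the assumed correlations.

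The cost is wording only: no extra participants, and no loss of power for the sized test. The real downside is that EV cargo can be confirmatory only when distress is significant, and the authors already regard that outcome as possibly underpowered. If the sponsor wants EV cargo to stand on its own, splitting alpha at 0.025 each is the alternative. Under the formula that reproduces 84, that needs 100 participants before dropout, or leaves distress with power 0.71 at 84.

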**Table 4 Tab4:**
[figure not shown]
Schedule of enrolment, interventions, and assessments

*Note*. *BaSIQS* Basic Scale on Insomnia complaints and Quality of Sleep, *CA* cancer antigen, *CCI* Client Change Interview, *CEA* carcinoembryonic antigen, *CORE-OM* Clinical Outcome Routine Evaluation - Outcome Measure, *CRP* C-reactive protein, *DASS-21* Depression, Anxiety Stress Scales-21, *DT* distress thermometer, *ERQ* Emotion Regulation Questionnaire, *FCR-7* 7-item Fear of Cancer Recurrence, *FFMQ* Five-Facet Mindfulness Questionnaire, *FTND* Fagerström Test for Nicotine Dependence, *IFN-γ* interferon gamma, *IL* interleukin, *IPAQ-SF* International Physical Activity Questionnaire - Short Form, *MBCT* mindfulness-based cognitive therapy, *PSA* prostate-specific antigen, *PTGI* Posttraumatic Growth Inventory, *SSSS* Satisfaction with Social Support Scale, *TAU* treatment as usual, *TNF* tumour necrosis factor, *W* weeks, *WHOQOL-Bref* World Health Organization Quality of Life – Bref

For each self-report measure, the total score obtained for scale and/or subscales will be used as outcomes. Measures examining the eligibility criteria and the sociodemographic and health-related information are also reported in Table 3.

To determine EVs cargo, total EVs will be isolated from platelet-free plasma samples by ultracentrifugation, followed by a purification step for CNS-derived EVs by immunoprecipitation with CNS-specific antibodies. Since we are interested in CNS-derived EVs, brain-related microRNAs will be measured to verify the origin of the EVs. This is achieved by isothermal nucleic acid amplification method. Results are measured by luminescence.

To evaluate the biochemical markers, inflammatory response biomarkers (IL-1, IL-6, IL-8, IL-10, IFN-γ, TNF) will be detected in serum by multiplex immunoassay (MILLIPLEX® Multiplex Assays Using Luminex®). Similarly, various cancer antigens (CA 15-3 and CA 19.9 in units/mL, PSA in ng/mL, CEA in ng/mL) will also be detected by immunoassay to monitor cancer recurrence. Other health-related biomarkers will include c-reactive protein (mg/L), telomerase activity, erythrocyte number (million/mm^3^), adrenocorticotropic hormone (pg/mL via immunoassay analyser), and glycosylated haemoglobin (mmol/mol via high-performance liquid chromatography).

### Assignment of intervention

#### Allocation

Participants will be randomly assigned to one of the two arms: MBCT or TAU groups (1:1 allocation ratio). Randomization blocks will be created using informatic tools and the entire process will be overseen by an investigator who will not be directly involved in the intervention or assessments. This investigator will inform the research team of the final allocation of each participant.

#### Blinding

Prior to randomization, individuals involved in the study (participants, study coordinators, mindfulness instructor(s), research assistants, statistician) will be blinded to the study conditions. After randomization, the research team will inform participants about group membership. Similar to previous studies in the field [14], and given the specificities and resources available in the current study, it is impossible to guarantee further blinding of participants and staff irrespective of their role. This unblinding also applies to the data analysts as most of the team members involved in the data collection will participate in the data management and analysis. Even so, the team members not collaborating directly in the data collection, such as the team dedicated to the characterization of the CNS-derived EVs, will be blinded to the study conditions where possible.

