### Data collection and management

After registration, participants will be assigned randomly generated identification codes. They will be asked to keep and use the code to avoid inserting sensitive personal data during their participation. Correspondence between the code and participant’s personal information (e.g. name; contact information; clinical identification in IPOP) is stored in a metadata file that is encrypted with a password and accessible only through the IPOP’s computer, which is protected by institutional security measures.

Data on sociodemographic and health self-report, screening, and primary and secondary outcome measures will be stored in the online survey service used here, LimeSurvey, which adheres to user privacy policies. Data will be periodically copied to an IPOP computer, where they are processed and inserted into excel files. These files will only be accessible to members of the IPOP research team via passwords or physical keys to open specific doors in the case of paper-based documentation, which will be kept in cabinets and locked.

Biological marker data will be obtained from blood samples collected from participants using a 21- to 23-gauge needle into 3 EDTA tubes (≤ 12 mL) and 1 nonadditive tube (4 mL). The standard tubes are stored at 4 °C for a maximum of 180 min. Tubes will be centrifuged at 2500*g* for 30 min at 4 °C. The upper third of plasma will be transferred to sterilized 2 mL tubes, and the plasma samples will be aliquoted and stored at − 80 °C in the hospital biobank until further use. The tubes will be labelled with a reference to the MindGAP project and a participant identification code to ensure anonymization during the blood collection and processing. Prior to EV isolation, a centrifugation step at 5000*g* for 15 min is performed in thawed plasma samples, to remove most of the remaining platelets.

For both self-reported and biological data, a privacy impact assessment has already been submitted, analysed, and approved by the IPOP’s Data Protection Officer.

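### Analysts are left unblinded for a staffing reason and laboratory blinding is promised only where possible: a disclosed but avoidable risk of bias that coded data and the allocation investigator could reduce

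*Protocol article*

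**What the plan says.** All of this comes from the protocol article.

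- **Blinding.** Before randomization, participants, coordinators, instructors, research assistants and the statistician do not know the arm. Afterwards, citing the features of the study and its resources, the section states that "it is impossible to guarantee further blinding of participants and staff irrespective of their role". It then says: "This unblinding also applies to the data analysts as most of the team members involved in the data collection will participate" in managing and analysing the data. One exception follows: members not directly collecting data, "such as the team dedicated to the characterization of the CNS-derived EVs, will be blinded to the study conditions where possible".
- **Allocation.** Randomization is "overseen by an investigator who will not be directly involved in the intervention or assessments". The section continues: "This investigator will inform the research team of the final allocation of each participant".
- **Data collection and management.** Participants receive random codes so that they need not enter personal details. For blood samples, "The tubes will be labelled with a reference to the MindGAP project and a participant identification code to ensure anonymization". The data files are open to the hospital research team.
- **Statistical methods.** Each outcome has a linear mixed model with a group-by-time interaction and a random participant effect. Error screening comes first. Baseline differences between groups may lead to adjustment of the primary analyses. Residual normality is judged by eye from Q-Q plots. MBCT participants with fewer than four sessions are left out.

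**The concern.** One of the two primary outcomes, the DASS-21 total, is self-rated by people who know which arm they are in, and nothing in the analysis can undo that. Masking the laboratory and the analysts is the main further safeguard that the design could still add. The protocol gives up the analyst part for an organisational reason and makes the laboratory part conditional.

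The choices left open then fall to people who know the arms: which entries count as errors, which baseline differences justify adjustment, and whether a residual plot is acceptable. Each can be made in good faith and still lean towards the expected result. Oversight and monitoring provides no data monitoring committee, no steering committee and no formal audit, so no outside body is named that would review these choices.

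**Working it through.** The protocol gives no figure on this point, so the first three steps compare its sections.

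**1. Is the stated obstacle inherent?** Participants cannot be masked to a group mindfulness programme, and the team must know the arms to inform participants and run the groups. The reason given for the analysts is different: the same people collect and analyse. The Blinding section itself treats masking as depending on role, because it plans masking for the EV team.

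**2. Do the existing arrangements already mask anyone?** Not the analysts.
- The codes serve privacy. The hospital team can open the files and is also told each allocation, so a code does not hide the arm from it.
- The investigator outside intervention and assessments does not keep the allocation to themselves.
- The rule on fewer than four sessions can apply only to MBCT. Attendance and home-practice fields therefore reveal the arm.

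Relabelling arms A and B under the existing codes would thus not be enough. Masking needs new analysis IDs and removal of the MBCT-only fields. The existing investigator is placed to do both.

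**3. Is there discretion for masking to protect?** Yes: error screening, the decision on covariates after comparing groups, and the Q-Q judgement. The DASS-21 total score and the basic form of the mixed model are already fixed.

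**4. Illustration of size (assumptions, not protocol inputs).** Suppose k defensible variants of one analysis give test statistics Z_i = √r·U + √(1−r)·E_i, with U and E_i independent standard normal, and the most extreme is kept. With c = 1.96 and no true effect:

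- either direction: 1 − ∫ φ(u) [Φ((c − √r·u)/√(1−r)) − Φ((−c − √r·u)/√(1−r))]^k du
- MBCT-favouring direction only: 1 − ∫ φ(u) [Φ((c − √r·u)/√(1−r))]^k du

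| r | k | Either direction (nominal 5%) | MBCT-favouring (nominal 2.5%) |
|---|---|---|---|
| 0.80 | 3 | 9.8% | 4.9% |
| 0.80 | 5 | 12.7% | 6.4% |
| 0.90 | 3 | 8.4% | 4.2% |
| 0.90 | 5 | 10.2% | 5.1% |
| 0.95 | 3 | 7.3% | 3.7% |
| 0.95 | 5 | 8.5% | 4.2% |
| 0.98 | 3 | 6.5% | 3.2% |
| 0.98 | 5 | 7.1% | 3.6% |

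These values come from numerical integration. Simulation of the r = 0.8 and 0.9 cases agrees to within about 0.1 percentage point. The right-hand column fits the worry better, since the fear is a lean towards MBCT.

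**The case against.** The strongest reply is that the protocol is candid and partly protective. It says that further blinding cannot be guaranteed, names its resource limits, and plans masking for the EV team, which covers the assay of one of the two primary outcomes. Self-completed online surveys, mandatory fields, a fixed total score and a named model already narrow the discretion. Dated scripts and key-release steps commonly belong in an analysis plan, which is not shown.

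Much of this stands, and it rules out several stronger readings:

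- **That the protocol calls blinding beyond participants impossible.** It says blinding cannot be guaranteed, then plans an exception.
- **That bias is built in.** The text shows a risk. Nothing in it demonstrates bias.
- **That blinding before randomization is worthless.** Baseline questionnaires and blood collection precede randomization (Intervention procedures), so not knowing the coming arm protects enrolment and baseline assessment.
- **That the instructors will analyse the data.** The text names data collectors only.
- **That an independent person alone holds the allocation.** It is passed to the research team.

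The illustration also measures undisclosed choice among analyses, not unblinding itself, and the number and correlation of variants have no source in the protocol.

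The point about the analysis plan does not remove the finding. The protocol is not silent here: it decides that analysts are unblinded. Disclosure is honest, but it does not justify a gap that existing arrangements could narrow.

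**Conclusion.** The point holds as an avoidable, disclosed risk of bias that is worth correcting. The analysts' unblinding follows from staffing, laboratory masking is conditional, and real discretion remains with people who know the arms.

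Its size cannot be established from the protocol. Under the assumed three to five variants at correlation 0.8 to 0.9, a nominal two-sided 5% becomes about 8-13%, and a nominal 2.5% favouring MBCT becomes about 4-6%. Higher correlation gives less. These figures show what free choice among variants could do and do not estimate bias in this trial.

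**What to change.** Amend the Blinding section as follows.

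1. The investigator who oversees randomization gives the analysts the uncleaned outcome dataset, with participant codes replaced by fresh analysis IDs and arms labelled A and B. Attendance, home-practice and other MBCT-only fields are removed.
2. Any attendance-based rule in Statistical methods is applied by that investigator, apart from the masked dataset.
3. Cleaning decisions, the choice of covariates, the model script and the residual checks are completed and dated on the masked dataset. Only then is the key released.
4. For the laboratory, state that all T1, T3 and T4 samples (EV, cytokine and other assays) are run under code, with no arm information sent to laboratory staff. This replaces the conditional wording.

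The cost is protocol wording and a small amount of work for an investigator already in post. Masking will be imperfect where team members can recognise an individual participant's data, and the amendment should say so.
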